In the present feasibility study, the Attention Restoration Theory informs the conceptual rationale for using immersive VR-based forest exposure in long-term care. The primary goal of VR-based nature interventions is to provide visual nature experiences to long-term care residents despite mobility limitations, thereby supporting their well-being and potentially preventing outcomes such as sleep disturbances, affective disorders, loneliness, and reduced trust in nursing staff. The study focuses on feasibility, acceptability, and implementation in routine care, while exploratory questionnaire data will describe changes in sleep quality, anxiety and depressive symptoms, subjective wellbeing, loneliness, and trust in nursing staff.

Figure 1 illustrates the assumed pathways of the VR-based nature intervention. The immersive forest videos are expected to provide a restorative nature experience through soft fascination, attentional restoration, relaxation, distraction, and perceived presence. These processes may contribute to exploratory changes in sleep quality, anxiety and depressive symptoms, subjective wellbeing, and loneliness. In joint sessions with nursing staff, the shared VR experience may additionally support interpersonal connection and trust in nursing staff. The primary focus of the present study is feasibility and acceptability, including adherence, barriers and facilitators, safety, and implementation within long-term care routines.

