Five out of 10 residents will complete one VR session per week together with a member of the nursing staff^1^. The participating staff member may vary between sessions depending on shift schedules, workload, and availability. This approach reflects real-world long-term care routines, where residents are commonly supported by several members of the nursing team. Accordingly, trust is conceptualized as residents' perceived trust in nursing staff more broadly. The qualitative interviews will explore how residents and nursing staff perceive the joint sessions, including whether shared VR experiences influence interpersonal connection, perceived support, and trust in nursing staff under routine care conditions.

The remaining four residents will conduct the sessions independently following an initial briefing and instructions from nursing staff. Residents receive a personal VR headset for the duration of the intervention and complete the sessions before bedtime in an upright position in bed or another seated position.

The VR system is preconfigured to minimise handling steps. Specifically, the VR headsets will be fully configured by the research team before use. Residents are not expected to navigate the standard Meta Quest menu or select videos independently. Instead, the respective intervention video will be preselected and started by nursing staff after instruction. Thus, residents only need to wear the headset and experience the video, while technical handling is kept to a minimum. For joint sessions, nursing staff will use shared VR headsets, which require a short calibration phase before each session.

At the beginning of the intervention period, an information session with hands-on training is held with participating residents and nursing staff to explain the use of the VR headsets, outline the course of the intervention, and address any questions. Usual care and daily routines within the long-term care facilities, regular medication, therapeutic procedures and social activities may continue unchanged during the intervention period.

After each use, the VR headsets and contact surfaces will be cleaned and disinfected according to the facility's hygiene standards.

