**Figure 3 F3:**
[figure not shown]
Participant timeline. The inclusion to the study includes an eligibility screening, the informed consent to participate and the qualitative purposeful sampling to intervention groups. Blue boxes mark quantitative and orange boxes qualitative assessment. The time points for data collection are: before the start of the intervention (T0), 2 weeks after the start (T1) and after the end of the intervention (T2).

All participants will be selected according to maximal variation sampling criteria to ensure a broad perspective on the research questions (40).

Maximal variation sampling will be applied pragmatically within the eligible pool available in the two participating facilities. The aim is to include a range of perspectives that are relevant for assessing feasibility and acceptability in a real-world long-term care setting. For residents, variation will be sought with regard to age, gender, and degree of mobility. For nursing staff, variation will be sought with regard to age, gender, and work experience. The exact number and socio-demographic composition of eligible residents and staff will depend on the participating facilities and will be documented during recruitment. Basic information on the available recruitment pool and the socio-demographic characteristics of included participants will be reported in the feasibility study.

Afterwards, residents will be assigned into two groups, aiming for an equal distribution of characteristics:
(1)“Residents completing a weekly VR session together with a nurse” and(2)“Residents conducting the sessions independently after initial instruction”.

In the joint sessions, nursing staff actively participate by watching a 360° video with the VR headset together with the resident. In addition, they may provide support if the resident encounters difficulties with the device or procedure. Including participants from two separate facilities as well as the variation between individual and joint sessions with nursing staff allows the exploration of contextual variability. The sample is adequate to inform adjustments to the study design and intervention for a subsequent RCT.

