##### Intervention diary

3.4.2.6

Moreover, a self-developed intervention diary will document session frequency and duration, whether sessions were conducted independently or with nursing staff, and any technical difficulties, interruptions or early termination. To capture immediate perceived responses to individual VR sessions with minimal participant burden, will rate their overall session experience on a 5-point scale ranging from 1 (“very unpleasant/not acceptable”) to 5 (“very pleasant/very acceptable”) and may note spontaneous impressions or notable experiences directly after the session. In addition, the overall dropout rate will be recorded.

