### Monitoring and safety

5.5

Participation in the feasibility study Nature Boost may be discontinued due to intolerable adverse reactions (e.g., dizziness, nausea, disorientation), serious health events that pose a significant health risk or require hospitalisation and externally triggered safety concerns as a manufacturer-initiated technical recall of the VR headset. Also, participants may withdraw voluntarily at any time without providing a reason. All discontinuations will be carefully documented and affected participants will receive medical attention if needed. Early withdrawal from the study will have no negative consequences for participants. In cases of mild and isolated symptoms as dizziness, participants may be offered the option to resume participation after a short break, provided no medical concerns persist and they explicitly consent. Any withdrawal or protocol deviation and its reason will be recorded, and all data collected up to that point will be included in the analysis.

Adverse events (AEs) will be systematically monitored throughout the study. The research team will do regular check-ins and residents are observed by nursing staff. Additionally, all participants are free to report symptoms at any time via phone or email to the research team. Documentation will be completed by a trained member of the research team using the designated reporting form. All AEs will be assessed in terms of severity, duration, and their potential relationship to the study intervention. Depending on the nature of the event, appropriate actions will be taken by the study team, such as recommending a medical consultation, adjusting the intervention, or discontinuing study participation if necessary. Serious adverse events (SAEs) will be reported within 24 h of detection or notification. Final assessment, decisions regarding further actions, and compliance with reporting requirements lie with the study management. If needed, an additional medical evaluation will be obtained. All steps will be taken in accordance with applicable regulatory standards and Good Clinical Practice (GCP).

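### Adverse-event monitoring is called systematic, but no symptom question is described after each VR session, so mild or short-lived cybersickness may be under-ascertained

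*Protocol article*

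**What the plan says.** The Introduction (section 1) places safety inside the study's primary focus on feasibility and acceptability, "including adherence, barriers and facilitators, safety, and implementation within long-term care routines".

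Section 5.5 (Monitoring and safety) states: "Adverse events (AEs) will be systematically monitored throughout the study". It then names the channels. Two share one sentence: "The research team will do regular check-ins and residents are observed by nursing staff". The third is voluntary: "all participants are free to report symptoms at any time via phone or email to the research team". Recording is also covered: "Documentation will be completed by a trained member of the research team using the designated reporting form", with severity, duration and relationship to the intervention assessed. The same section gives dizziness, nausea and disorientation as examples of reactions that may lead to discontinuation.

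Two other sections show what staff are doing during a session. In joint sessions, "nursing staff actively participate by watching a 360° video with the VR headset together with the resident" (section 3.3, Sampling); they may also help a resident who runs into difficulty. More generally, "the respective intervention video will be preselected and started by nursing staff after instruction" (section 3.2, Intervention).

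Sections 3.2 and 3.4.2.6 describe the diary. It is completed after each session and holds the date, duration, individual or joint format, whether a staff member was present, reasons for a missed or incomplete session, "any technical difficulties, interruptions or early termination", one five-point rating of the session, and optional comments.

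**The concern.** A method of ascertainment is systematic when every participant is asked the same thing at defined times. On the description given, none of the three channels does this session by session. Check-ins are regular, but at no stated interval. Observation depends on a staff member being there and able to see the resident. Phone and e-mail reports depend on the resident choosing to make contact. The one instrument that does reach every session, the diary, lists no field for the symptoms that section 5.5 itself names.

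The gap concerns a particular kind of event: a resident feels dizzy or queasy for a few minutes, finishes the video and says nothing unprompted. Tolerability is among the main things this study passes to the later randomised trial. A low symptom count would be hard to read if one could not tell whether residents had no symptoms or were not asked. A transient symptom from week one is also difficult to recover in an interview after week four.

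**Working it through.** The article states no adverse-event rate or capture rate, so there is no figure to reproduce. The check is a session count from the article's own schedule, followed by a comparison of the described sources.

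**Inputs**
- Residents: 10 (section 3.3).
- Sessions per resident: 3 per week × 4 weeks = 12 (Abstract; section 3.2).
- Residents with one joint session per week: 5 in section 3.2, 6 in the Abstract. Section 3.2 then gives the independent group as the remaining four, and 5 + 4 = 9, not 10. These passages need reconciling; both values are carried here.

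**Session count**
- Total planned: 10 × 12 = 120.
- Joint, with 5 residents: 5 × 4 = 20 (20/120 = 16.7%), leaving 120 − 20 = 100 (83.3%).
- Joint, with 6 residents: 6 × 4 = 24 (24/120 = 20.0%), leaving 120 − 24 = 96 (80.0%).

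**What the text provides in each type of session**

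| Session type | Planned number | Staff role as described |
|---|---|---|
| Joint | 20 to 24 | Present, wearing a headset; may help with difficulties |
| Other | 96 to 100 | Start the video; no statement that they stay |

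For the second row, staff presence is a diary field, so it is treated as something that varies. One exception is stated: after a session that could not be completed, the next is supported by staff (section 3.2). The schedule alone does not show how many sessions that would be.

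**What each source would show for a brief symptom in a completed session**
- Diary: no symptom field listed; the early-termination and incomplete-session fields do not apply; a low rating or a comment might hint at it.
- Staff observation: limited by a headset in joint sessions, not assured in the others.
- Check-ins: could elicit it, depending on timing and on questions that the article does not show.
- Phone or e-mail: only if volunteered.
- Reporting form: records an event once it is known; it does not find one.
- Questionnaires (section 3.4.2): sleep, well-being, loneliness, anxiety and depression, and trust; none measures VR symptoms.
- T2 interviews (section 3.4.1): cover headset experience and barriers, and ask staff about changes in residents during or after sessions; no symptom question is named, and recall can reach back four weeks.

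Several sources could catch the event. None is described as asking about it after each session.

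**The case against.** The strongest reply is that monitoring has several layers. The sentence that mentions staff observation begins with research-team check-ins, and section 5.5 adds self-report and a form completed by a trained team member. Dizziness and nausea are felt more than seen, so an observer's view matters less than whether the resident can speak up. Residents with even mild cognitive deficit are excluded, and those included must be able to take the headset off unaided. Staff are there when the video starts, and in joint sessions they take part with the resident and can respond. The check-in questions, the form and the diary page are not reproduced, and a condensed article may leave them to the full protocol.

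Much of this stands, and it rules out several stronger readings that a reader might infer:
- That monitoring rests on nursing staff alone. Section 5.5 says otherwise.
- That symptoms will certainly be under-counted, or by a calculable amount. The documents give neither a symptom risk nor a capture rate, so any percentage would come from assumption.
- That capture will differ between joint and individual sessions. Nothing shows this, and section 3.5.2 plans summaries overall and by site, not by session format.
- That the absence of an adverse-event table from section 3.5.2 is a defect. Such a table may sit in an analysis plan that is not shown.

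The reply does not remove the point about the diary. Its content is described in two sections, field by field, and symptoms are not among the fields. Residents' ability to report is a reason to ask them, not a substitute for asking.

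**Conclusion.** The point holds as a risk of incomplete ascertainment, confined mainly to mild or transient symptoms in sessions that are completed. The word systematic in section 5.5 is not backed by any described symptom question after each session, in a study that counts safety within its primary focus. Staff are in a headset for 20 to 24 of 120 planned sessions, and no requirement to stay is stated for the other 96 to 100.

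This rests on two assumptions: that the diary page matches the fields listed in sections 3.2 and 3.4.2.6, and that check-ins do not follow every session. If the actual page already carries symptom items, only the wording of the article needs correcting. Events that stop a session or lead to discontinuation are reasonably covered by the existing fields and by section 5.5. The change should be made before the first session; nothing here calls the study itself into question.

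**What to change.** 1. On the diary page completed after each session, add fixed yes/no items for dizziness, nausea, disorientation and 'other'. Residents answer after every session; staff answer for themselves after joint sessions. That gives 120 planned resident pages and 20 to 24 staff pages.
2. In section 5.5, name these items as a systematic source of adverse-event information, alongside research-team check-ins and staff observation.
3. Report, for each symptom, the number of residents with at least one occurrence and the number of sessions affected, as descriptive counts. Do not put binomial intervals on the session counts: the 120 sessions are clustered within 10 residents and are not independent.

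The cost is four tick boxes, a sentence in section 5.5 and a short table. Completion takes under a minute per session. Prompted items will also produce a higher symptom count than volunteered reports, so the report should say that symptoms were actively asked about.

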## Appendix

1. TIDier Checklist
2. SPIRIT Outcomes 2022 Checklist (for combined completion of SPIRIT 2013 and SPIRIT Outcomes 2022 items)
